### Safety Outcomes

The safety outcomes will include any adverse events and clinically meaningful changes in vital signs or laboratory parameters during the trial. Participants will be asked to report any abnormal reactions occurring during the trial to the investigators. At week 6, participants will undergo liver function and renal function tests to monitor hepatotoxicity and nephrotoxicity.

### Adverse Events Management

All details of related and unexpected adverse events, including time of occurrence, degree and duration, suspected causes, and effective measures and outcomes will be recorded. The investigators will immediately take appropriate treatment measures for the participants, report and follow-up, and assess the relatedness of the event to the study drug from a clinical point of view. Any adverse event will be treated suitably and recorded accurately and completely. The causality between adverse events and intervention will be assessed by a causality assessment tool, the World Health Organization-Uppsala Monitoring Centre (WHO-UMC) case causality assessment, to evaluate the likelihood that an adverse event is associated with the intervention. The causality assessment will be accomplished by a combined assessment taking into account the clinical-pharmacological aspects of the case history and the quality of the documentation of the observation with a table of predefined statements and classifies events as the following categorization: certain, probable/likely, possible, unlikely, and two sub-categories: conditional/unclassified (when information pending), and unassessable/unclassifiable (when sufficient information is not available).

### Data Collection and Management

Data will be collected at baseline, at 14, 28, 42, and 56 days post-allocation, and at the 90 days follow-up. To promote data quality, each site’s investigator will be trained centrally regarding the study requirements, including standardized evaluation of scales involved in the trial, operation of the CM tongue and facial imaging and analysis instrument, requirements for serum specimen collection, and on eliciting information from participants in a uniform and reproducible manner.

An electronic data capture system will be used in this study. The investigator/clinical research coordinator (CRC) will input the original data into the electronic data capture system accurately, in a timely, complete, and standard manner. After data entry, data may not be changed at will. If data entries need to be modified, the investigator/CRC will need to record the reason for modification according to the system prompt. All the operations in the system are traceable.

The data manager will develop a detailed data verification plan according to the protocol and case report form, including logic verification, scope verification, time window verification, consistency verification, and compliance verification. The efficiency indicators and key safety indicators should be fully verified to ensure the accuracy and integrity of the data. Data verification should be carried out in the case of an unknown test group, and the generated data query content should avoid deviation or induced questions.

After all the data are inputted and queried, a blind review meeting will be held to determine the data set division. After reaching a consensus on all data questions, the sponsor, principal investigator, data manager, and statistician will jointly sign the approval document for locking the database. After obtaining approval, the data manager will execute the database locking operation and remove the system operation authority of the relevant personnel. The study documents will be retained in a secure location for at least 5  years after trial completion.

### Quality Control and Data Monitoring

The trial is managed by the Dongzhimen Hospital, Beijing University of Chinese Medicine. The protocol compliance, safety, and the trial data will be supervised by the Data and Safety Monitoring Board (DSMB), an independent group of experts that advises funding agencies and study investigators. DSMB members include experts from different fields (Western Medical Sciences, Chinese Medicine, Clinical Epidemiology, and Statistics). An auditing will be conducted twice a month during the enrollment period and every month during the follow-up period, and the process will be independent from investigators.

### Statistical Methods

Statistical analysis will be performed using Statistical Analysis System version 9.4 (SAS Institute Inc., Cary, North Carolina, United States) statistical software packages. Outcome measurements will be analyzed using full analysis sets and per protocol sets according to intention-to-treat (ITT) analysis. Safety analysis will be performed in a safety set, which is defined as a subset of subjects who received at least one treatment and had actual safety indicators record data. The statistical analysis will include baseline characteristics of participants, compliance and concomitant medication, efficacy analysis and safety analysis. For continuous data, we will describe the results using the mean (standard deviation, SD), maximum, minimum, median and non-parametric test median (quartile deviation, QD). Categorical data will be described as absolute values and proportions. For continuous outcomes, paired *t*-test or Wilcoxon signed-rank test will be used to analyze significant differences between baseline and each time point. The Wilcoxon rank-sum test will be employed for comparisons between treatment groups. Chi-squared test will be used for categorical data and Wilcoxon rank-sum test will be used for ranked data. Analysis of covariance (ANCOVA) will be used to control potential confounding variables.

We will use a two-sided 5% significance level and 85% power. Baseline characteristics in each group will be analyzed using descriptive statistics. Compliance analysis will be based on full analysis sets, and analysis of concomitant medications will be based on safety sets. Regarding the primary outcome variable, between-group comparisons of the change in syndrome score will be analyzed between pre- and post-treatment using paired t-test or Wilcoxon signed-rank test. As to the secondary outcomes, comparisons of the changes in NIHSS score in sub Trial I, the Seattle Angina Questionnaire score in sub Trial II, and the Toronto Clinical Scoring System in sub Trial III, will be analyzed using paired t-test or Wilcoxon signed-rank test between baseline and each time point. The Wilcoxon rank-sum test will be employed for comparisons between treatment groups. Any factors impacting efficacy, such as age and sex, should be taken into account as covariate. Safety will be analyzed in terms of all the adverse events occurred during the trial, and the incidence will be compared between groups using the chi-squared test or Fisher’s exact probability method.

Last observation carry forward (LOCF) approach will be used to impute missing data of primary outcome according to intention-to-treat analysis. A sensitivity analysis will be conducted to determine the robustness of the results under the missing at random assumption, to evaluate the role of lost to follow-up (i.e., participants who did not follow-up to V4), by using the LOCF method. And a *p* value of less than 0.05 will be considered statistically significant.

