Among the herbs cited above, Hedysarum polybotrys Hand.-Mazz. contributes to regulating Qi. According to the Chinese medicine compatibility theory of “sovereign, ministerial, adjuvant and messenger”, the Hedysarum polybotrys Hand.-Mazz is sovereign herb in the BQTL, and it also showed pharmacological activity in well designed experiments. Hedysarum polybotrys polysaccharide (HPS) has significant protective effect against heart and brain hypoxia (Dong et al., 2013). It can protect the endomembrane barrier (Wang et al., 2013), promote peripheral nerve regeneration and improve the recovery of nerve function (Wei et al., 2009), and enhance nerve amplification effect by encouraging proximal axons to grow more lateral buds and effectively improve peripheral nerve (Wang et al., 2013). Panax notoginseng saponins (PNS) is isolated from the roots and rhizomes of Panax notoginseng (Burkill) F.H.Chen, a highly valued Chinese materia medica with the efficacy of promoting blood circulation and removing blood stasis. PNS has been shown to exert strong anti-inflammatory effects against atherosclerosis-related cardiac-cerebral vascular disease (Wan et al., 2009). A new study also suggested that PNS exerted long-term neuroprotective effects that assisted in stroke recovery (Zhou et al., 2021). PNS ameliorates diabetic peripheral neuropathy by attenuating electrophysiological, circulatory and morphological alterations (Hao et al., 2017).

Taken together, BQTL herbal formulae has been widely used to treat multiple diseases involving the QDBS syndrome. However, no large, randomized trial has studied the effect of BQTL granules on QDBS syndrome. The aims of this basket randomized controlled trial (RCT) are firstly to optimize parameters and examine the feasibility of a subsequent phase III RCT through preliminary evidence on the clinical efficacy and safety of BQTL granules on three diseases (ischemic stroke, stable angina pectoris, and diabetic peripheral neuropathy) involving QDBS syndrome, as compared with placebo. Secondly, it aims to elucidate the mechanism by which BQTL granules exert an effect on QDBS syndrome.

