## Materials and Methods

### Study Design

The BuqiTongluo granule for Qi deficiency and blood stasis syndrome (BOSS) study is a basket herbal trial studying the effect of BQTL granules across multiple cohorts of three diseases (ClinicalTrials.gov, NCT04408261). The BOSS protocol includes three multicenter randomized, double-blinded, placebo-controlled sub trials that will study BQTL granules in three independent patient populations: ischemic stroke (sub trial I), stable angina pectoris (sub trial II), and diabetic peripheral neuropathy (sub trial III). This study is currently open at 14 sites across China. In each sub trial, patients will be randomly divided into an intervention group (BQTL granule) and placebo group (placebo) using an 1:1 allocation ratio, adhering to the Standard Protocol Items: Recommendations for Interventional Trials (SPIRIT) statement (Chan et al., 2013). The study period includes 6 weeks of medication and 90 days of follow-up. The study procedure is summarized in the CONSORT diagram (Figure 1), and the schedule of enrolment, interventions, and assessments is summarized in Table1. The trial will be performed in accordance with the Declaration of Helsinki and Good Clinical Practice Guidelines. Informed consent will be obtained from all participants.

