### Sample Size

For a main phase II trial assessing natural drugs, according to the NMPA recommendation (No. 28, 2007 and No. 109, 2018) and data from our pilot study, the sample size should not be less than 60 per treatment arm for each disease to estimate the parameter. We enrolled 432 participants to allow for dropouts.

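### The trial is sized to estimate parameters for phase III, but the primary outcome is analysed by tests read at 0.05, and no analysis is named to give the between-arm difference with its interval

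*Protocol article*

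**What the plan says.** All references are to the protocol article.

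- **Aim.** The Introduction puts first "firstly to optimize parameters and examine the feasibility of a subsequent phase III RCT through preliminary evidence on the clinical efficacy and safety" of the granules in the three diseases, compared with placebo.
- **Size.** Sample Size refers to regulatory recommendations and pilot data, and concludes that "the sample size should not be less than 60 per treatment arm for each disease to estimate the parameter". It adds: "We enrolled 432 participants to allow for dropouts". Study Design says that patients in each sub trial are "randomly divided into an intervention group (BQTL granule) and placebo group (placebo) using an 1:1 allocation ratio".
- **Primary outcome.** This is the change in the QDBS syndrome score (range 0 to 51) over the 6 weeks of treatment. For it, the second paragraph of Statistical Methods announces a between-group comparison but names a paired t-test or Wilcoxon signed-rank test.
- **Comparison of arms.** The first paragraph of Statistical Methods says "The Wilcoxon rank-sum test will be employed for comparisons between treatment groups". The second repeats this after the secondary outcomes.
- **Threshold.** "We will use a two-sided 5% significance level and 85% power"; a p "value of less than 0.05 will be considered statistically significant".
- **Other outputs.** Continuous data are summarised by mean (SD), median and range. ANCOVA is named as a means of adjusting for possible confounders, with age and sex as example covariates. No outcome, no full covariate list and no primary or supportive role is attached to it.

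No section names a between-arm difference, an effect size or a confidence interval.

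**The concern.** A phase III sample size needs two quantities from a phase II trial: the between-arm difference, with its uncertainty, and the SD of the outcome given the planned adjustment. The tests named for the primary outcome are not set up to deliver them. A paired t-test or signed-rank test asks whether patients changed from baseline within one arm, so it does not compare arms at all. A rank-sum test compares arms, but its p-value contains neither a mean difference nor an SD.

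At stake is whether the trial answers its own first question. If the headline for each disease is a p-value on one side or the other of 0.05, a non-significant sub trial may be read as evidence of no effect when the data are still compatible with a useful one. A significant sub trial may be carried forward at face value.

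**Working it through.** **1. Size per comparison.** 432 / (3 diseases × 2 arms) = 72 per arm. The stated minimum is 60 per arm, so 3 × 2 × 60 = 360. No dropout rate is given, so 432 cannot be derived from stated inputs alone. It follows from 60 / (1 − 1/6) = 72, or from 60 × 1.20 = 72.

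**2. What each named analysis gives.**

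| Analysis in Statistical Methods | Compares arms? | Planned to report a difference with interval? |
|---|---|---|
| Paired t-test or signed-rank (named for the primary outcome) | No | No |
| Rank-sum | Yes | No, p-value only |
| Mean (SD) summaries | Indirectly, if shown by arm | No; a crude difference can be calculated |
| ANCOVA | Yes, if treatment is in the model | It could; outcome and role not fixed |

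**3. Precision available.** The documents give no SD for QDBS change, so results are in SD units. Half-width of the 95% CI = 1.96 × √(2/n):

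- n = 72: 1.96 × 0.1667 = 0.33 SD
- n = 60: 1.96 × 0.1826 = 0.36 SD

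Adjusting for baseline would narrow these to the extent that baseline predicts the change. The documents give no correlation, so no gain is counted.

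**4. What 85% power corresponds to.** The stated power has no effect size attached. Detectable difference = (1.96 + 1.036) × √(2/n): 0.50 SD at 72 per arm and 0.55 SD at 60. Dividing by √(3/π) for the rank-sum test with normal data gives 0.51 and 0.56 SD.

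**5. If results were selected on p<0.05.** This selection rule is an assumption, and so are the true effects. With true effect d, standard error s = √(2/72) = 0.1667 and k = 1.96 − d/s, the chance of a significant result favouring BQTL is 1 − Φ(k). The mean estimate among such results is d + s × φ(k) / (1 − Φ(k)). A phase III trial sized for 85% power on that estimate needs 2 × (1.96 + 1.036)² / estimate² per arm, rounded up.

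| True effect (SD) | k | Significant | Mean significant estimate (SD) | Ratio to truth | Phase III n per arm | Its true power |
|---|---|---|---|---|---|---|
| 0.3 | 0.16 | 44% | 0.45 | 1.5 | 89 | 52% |
| 0.4 | −0.44 | 67% | 0.49 | 1.2 | 75 | 69% |
| 0.5 | −1.04 | 85% | 0.55 | 1.1 | 61 | 79% |

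These are normal approximations. Simulation with a t-test agrees closely (43% and 66% significant at 0.3 and 0.4 SD). Simulation of the rank-sum test itself at 60 per arm gives ratios of about 1.6, 1.3 and 1.15. Without selection, the mean difference is unbiased at every setting.

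**The case against.** The strongest case on the other side has four parts.

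*The ingredients are already planned.* ANCOVA with treatment in the model gives an adjusted difference, its standard error and a residual SD. Means and SDs by arm would allow anyone to work out a crude difference and interval. This stands as far as it goes: a reader might infer that the trial can produce only a rank-sum p-value, and the text does not support that. What remains is that no output is designated as the estimate, while the tests are.

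*Reporting of intervals is usually left to the analysis plan.* That is a fair general rule, and nothing in Statistical Methods forbids intervals. But the Discussion says that the article itself sets out a detailed analysis plan. The point is also not one of silence: methods are stated for the primary outcome, and they do not fit the stated aim.

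*Estimation is not the only aim.* The Abstract and the Introduction also speak of efficacy compared with placebo, and a 5% test is compatible with that. This is correct. The tests need not go; they should not be the main result.

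*Overstated effects are not a consequence of the plan.* A reader might infer that the rank-sum test inflates the effect, or that phase III will be sized on significant results. Neither is supported. The inflation comes from selecting on significance at limited power. The protocol says only what counts as statistically significant, and it makes neither phase III nor its size depend on that. With a true effect near 0.5 SD, which is about what 85% power detects at 72 per arm, the inflation is small.

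**Conclusion.** The mismatch is real but moderate. The size is justified by estimation, yet the analyses tied to the primary outcome are tests, one of which does not compare arms, and the model that could supply the estimate has no fixed outcome or role. This is an inexpensive improvement to a stated choice, not a flaw that invalidates the trial.

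Its firm size is the precision left unreported: about ±0.33 SD at 72 per arm and ±0.36 SD at 60 for each disease, before any gain from baseline adjustment. The overstatement factors of 1.5, 1.2 and 1.1 are conditional. They rest on normal data, on assumed true effects of 0.3, 0.4 and 0.5 SD that the documents neither give nor exclude, and on selection for significance. They are a reason to avoid that selection, not a prediction of what the sponsor will do.

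**What to change.** For each sub trial, state that:

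1. the main result is the between-arm difference in change in QDBS score at week 6 with its 95% CI, from an ANCOVA containing treatment and baseline QDBS score, with any further covariates listed in advance;
2. the residual SD from that model is reported alongside it;
3. the rank-sum test is supportive, and the paired t-test or signed-rank test only describes change within each arm, so that the between-group label is removed from it;
4. phase III planning uses the estimate, its interval and the SD, whether or not p<0.05.

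The cost is wording. No extra patients or measurements are needed: the baseline score is already required to form the primary outcome, and ANCOVA is already named. The downsides are that wide intervals become visible and the rank-sum test can no longer serve as the primary analysis. The change should be fixed and dated before unblinding.

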## Abstract

**Background:** BuqiTongluo (BQTL) granules are herbal phenotypic drugs for Qi deficiency and blood stasis (QDBS) syndrome. Its discovery relied primarily on knowledge of observable phenotypic changes associated with diseases. Although BQTL granules have been widely advocated by Chinese Medicine (CM) practitioners, its use lacks empirical support.

**Aim of the study:** In this basket trial, the efficacy of BQTL granules in multiple diseases that have the QDBS syndrome in common will be compared with placebo.

**Materials and Methods:** The BuqiTongluo granule for Qi deficiency and blood stasis syndrome (BOSS) study is a basket herbal trial (ClinicalTrials.gov, NCT04408261). It will be a double-blinded, randomized, placebo-controlled, parallel, multicenter, clinical trial. In total, 432 patients (1:1:1 ischemic stroke, stable angina pectoris, and diabetic peripheral neuropathy), who meet the operationalized diagnostic criteria for QDBS syndrome, have been recruited and randomized in a ratio of 1:1 to receive 6 weeks’ treatment with BQTL granules or placebo. The primary outcome is the change in the QDBS syndrome score at week 6 from baseline. Secondary outcomes include objective outcome measures for the three diseases and adverse events. Omics will help to understand these responses by molecular events.

**Conclusion:** QDBS syndrome is a common phenotypic marker that was hypothesized to predict whether patients with multiple diseases would respond to this targeted therapy. No previous basket trial has assessed the potential efficacy of an herbal intervention for multiple diseases. The unique promise of the trial is its ability to exploit a disease phenotype to discover novel treatments for three diseases for which the root cause is unknown, complex, or multifactorial, and for which scientific understanding is insufficient to provide valid molecular targets.

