### Primary Outcomes

The primary outcome of the study is improvement in QDBS syndrome, defined as a change in the national approved QDBS syndrome evaluation scale from before to after the 6-week treatment. The QDBS syndrome evaluation scale (Wang et al., 2015) was chosen because of its practical use in the evaluation of the QDBS syndrome. The scale is a 21-item clinician-rated scale with anchored item descriptions. It lists 21 clinical symptoms and physical signs related to the QDBS syndrome. The scale ranges from 0 to 51 with 51 indicating the worst score possible. The higher the score, the more severe the degree of the syndrome. The scale has been developed, validated, and applied in the Department of Neurology, Cardiology, Endocrinology, and multiple investigators have used this method to assess patients with QDBS syndrome. This scale has excellent inter-rater reliability and internal consistency. It is NMPA’s recommended outcome measure in Guideline for clinical research of new Chinese medicine drugs with syndrome.

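### The sentence on the primary outcome assigns a within-arm paired test to the BQTL-versus-placebo comparison and contradicts the plan's own general rule for between-group tests

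*Protocol article*

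**What the plan says.** The aim, in the Abstract, is that "the efficacy of BQTL granules in multiple diseases that have the QDBS syndrome in common will be compared with placebo". The design is stated there too: "It will be a double-blinded, randomized, placebo-controlled, parallel, multicenter, clinical trial". Study Design adds that in each sub trial "patients will be randomly divided into an intervention group (BQTL granule) and placebo group (placebo) using an 1:1 allocation ratio". Primary Outcomes gives the endpoint as improvement in the syndrome, "defined as a change in the national approved QDBS syndrome evaluation scale from before to after the 6-week treatment".

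Statistical Methods then deals with testing in two places.

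- **General paragraph, continuous outcomes.** The paired t-test or "Wilcoxon signed-rank test will be used to analyze significant differences between baseline and each time point". For the arms: "The Wilcoxon rank-sum test will be employed for comparisons between treatment groups". It adds: "Analysis of covariance (ANCOVA) will be used to control potential confounding variables".
- **Outcome-specific paragraph.** For the primary outcome: "between-group comparisons of the change in syndrome score will be analyzed between pre- and post-treatment using paired t-test or Wilcoxon signed-rank test". The next sentence gives the same paired tests to NIHSS, SAQ and the Toronto score, from baseline to each time point. Only after that is the rank-sum sentence repeated. Age and sex are then mentioned as examples of covariates.

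**The concern.** The only sentence that addresses the primary outcome by name calls the analysis a between-group comparison and then assigns tests that do not compare groups. Someone programming the primary analysis from that sentence would produce a p-value for change from baseline. That p-value mixes any drug effect with everything both arms share, such as placebo response and regression to the mean in patients selected for having the syndrome.

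The conflict with the general paragraph leaves open which test yields the primary p-value. If it stays open until the data are unblinded, the choice can follow the results.

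**Working it through.** **1. What each test can answer.** Let D be a patient's improvement in QDBS score over 6 weeks. Write its mean as μ + Δ under BQTL and μ under placebo, where μ is the shared improvement and Δ the drug effect.

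- Paired t-test in the BQTL arm: t = mean(D) / (SD/√n). Its null hypothesis is μ + Δ = 0.
- Two-sample comparison: mean(D, BQTL) − mean(D, placebo). Its expectation is (μ + Δ) − μ = Δ, so the shared part cancels.

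The trial's question is whether Δ = 0. The arms are independent, so the only pairs available are each patient's own two scores. The paired test therefore answers the trial's question only if μ = 0. The signed-rank test has the same limitation.

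**2. The two paragraphs side by side.**

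| Role | General paragraph | Outcome-specific paragraph, primary outcome |
|---|---|---|
| Baseline versus later, within arm | paired t or signed-rank | not separately stated |
| BQTL versus placebo | rank-sum | paired t or signed-rank |

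The second row is the contradiction. ANCOVA is named for covariate control and is not tied to the primary outcome.

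**3. Size of the consequence.** There is no plan figure to reproduce: the article gives no SD, expected change or effect size for the QDBS score. Inputs:

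- n = 72 per arm per disease: 432 / 3 / 2 (Abstract, Sample Size).
- n = 60 per arm per disease: the stated minimum (Sample Size).
- Two-sided 5% level (Statistical Methods).
- Assumed: Δ = 0, normal change scores, and a shared improvement m in units of the SD of change, shown as a range.

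Normal approximation for the BQTL-arm paired test (the opposite tail is negligible from m = 0.2 upward): P(significant) ≈ Φ(m√n − 1.96). With √72 = 8.485:

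- m = 0.2: Φ(1.697 − 1.96) = Φ(−0.263) ≈ 0.40
- m = 0.3: Φ(2.546 − 1.96) = Φ(0.586) ≈ 0.72
- m = 0.5: Φ(4.243 − 1.96) = Φ(2.283) ≈ 0.99

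Simulation with the t-test (20,000 trials per row; rank-sum on 5,000 of them), no drug effect:

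| Shared improvement (SD) | BQTL-arm paired test significant, n = 72 | Same, n = 60 | BQTL significant and placebo not, n = 72 | Two-sample t, n = 72 | Rank-sum, n = 72 |
|---|---|---|---|---|---|
| 0 | 5.0% | 5.2% | 4.7% | 5.0% | 4.3% |
| 0.2 | 38.5% | 33.9% | 23.6% | 4.9% | 4.9% |
| 0.3 | 70.6% | 62.8% | 20.2% | 4.9% | 5.1% |
| 0.5 | 98.7% | 97.0% | 1.2% | 4.9% | 4.6% |
| 0.8 | 100% | 100% | 0% | 5.0% | 5.0% |

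The between-group tests stay near 5% whatever the shared improvement. The paired test does so only when it is zero.

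**The case against.** The strongest reply is that this is a drafting slip. The QDBS score is a continuous outcome, so the general rule covers it. The rank-sum sentence appears twice, and its second appearance is not worded as limited to secondary outcomes. The disputed sentence itself speaks of between-group comparisons, and it may simply have merged the two steps of the general paragraph.

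Much of this stands. A reader might infer that the plan has no between-group test, or that the primary-outcome sentence overrides the general rule. The article does not support either: a valid test is named, and nothing says which paragraph prevails. Nor are three rival primary tests in play. ANCOVA is there for covariates, and the conflict is between the paired tests and the rank-sum test.

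The percentages also need care. A reader might take 99% as the trial's false-positive rate. It would be so only if efficacy were read from the BQTL arm alone, a rule the article does not state. At 0.5 SD the placebo arm would nearly always be significant too, and BQTL significant with placebo not occurs in 1.2% of trials. Among the values tried at n = 72, that pattern peaks at about 24%, at 0.2 SD.

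The reply does not remove the contradiction. The position of the repeated rank-sum sentence leaves its reach to the primary outcome unclear, and the sentence that names the primary outcome is wrong as written. This is a misstatement, not a detail left to a fuller document. The Discussion also says that the article presents a detailed statistical analysis plan.

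**Conclusion.** The point holds as an internal contradiction about the primary test. As worded, the primary-outcome sentence assigns a method that cannot compare BQTL with placebo. This needs no figure to establish.

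The rates of about 39%, 71% and 99% are conditional illustrations. They assume no drug effect, normal change scores, 72 per arm, shared improvements of 0.2, 0.3 and 0.5 SD, and a decision made on the BQTL arm alone.

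Two further inferences go beyond the documents. One is that the trial would yield no treatment difference for phase III planning: the plan includes summaries of continuous data and a between-group test, so a difference can be obtained. The other is that stroke patients enrolled 14–30 days after onset would improve on this score in any case: the article says nothing about spontaneous change in the QDBS score.

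**What to change.** Replace the primary-outcome sentence with one between-group analysis of the week-6 QDBS score. The preferred choice is the BQTL-minus-placebo difference from ANCOVA adjusting for the baseline score, with a 95% confidence interval and a two-sided p-value. It gives an estimate as well as a test, and it can take the covariates the article mentions, which a rank-sum test cannot.

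Keep the rank-sum test on the change score as the supporting analysis. It would also be a valid primary test, so preferring ANCOVA is a recommendation and not part of the error.

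Label all within-arm paired tests descriptive, for primary and secondary outcomes alike. State explicitly that the between-group rule covers the primary outcome, so that the two paragraphs agree.

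The cost is a few sentences in the statistical section and in any separate analysis plan. No new data are needed, since the baseline score is already collected. The change should be made and dated before unblinding. The article says that it precedes any data analysis, but it does not show the trial's present status.
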